## Methods and analysis

### Study design

This study is a preregistered randomised, longitudinal and monocentric project, led at the Hospital Maisonneuve-Rosemont (Montréal, Québec, Canada). This refers to a phase II randomised controlled trial according to the ORBIT (Obesity-Related Behavioral Intervention Trials) model.^49^ The goal of this type of study is to prepare the phase III study, investigating feasibility and acceptability of the study in terms of recruitment and adherence to the protocol and preliminary efficacy. According to the authors of this model, ‘pilot’ randomised trials are considered as a suitable methodology for this phase.

Recruitment of participants will be run from 1 May 2025 to 30 April 2026. Enrolment of participants will be managed by the research assistants responsible for the data collection. This study will evaluate the efficacy of an intervention combining VRH to alleviate pain in patients with hand arthritis. This study will also consider other clinical variables known to influence the experience of pain.

### Inclusion and exclusion criteria

The target population consists of individuals with inflammatory arthritis and osteoarthritis of the hands. Clubbing those two pathologies was chosen as a symptom of chronic pain, which is considered a transdiagnostic entity. Moreover, given participants are patients recruited on waiting lists in hospital, their inflammatory symptoms are controlled, leaving chronic pain at the forefront. This symptomatic approach appears reliable in this context.^50 51^ Participants will come from units of rheumatology or pain management of the Maisonneuve-Rosemont Hospital (Montréal, Québec, Canada). They receive standard medical care which can include medical treatment that will be reported among descriptive data. The inclusion criteria for both the experimental and the control group are: (a) being over 18 years old, (b) speaking and understanding French, (c) having a diagnosis of inflammatory arthritis or osteoarthritis causing invalidating chronic pain as reported by participants. The exclusion criteria include being unable to come to the hospital, having significant cognitive disorders (eg, dementia) impairing the capacity to understand and complete the questionnaires autonomously or having sensory impairments (ie, deafness, blindness) that impact the participation in the study.

### Measures

#### Primary outcome

The different dimensions of perceived pain levels will be measured using the Brief Pain Inventory–Short Form (BPI-SF).^52 53^ The BPI-SF is a self-administered nine-item questionnaire used to assess the impact of pain on patients' daily functioning. Participants are asked to rate the intensity of their worst, least, average and current pain on scales from 0 to 10, list ongoing treatments and their perceived effectiveness, and indicate the extent to which pain interferes with their usual activities. This questionnaire covers the sensory, emotional and functional aspects of the pain experience. This questionnaire has been shown to be reliable and valid in patients with osteoarthritis.^54^ The main criteria will be defined as the score of current perceived pain in the more painful hand with a higher score meaning a higher level of pain (for a psychometric justification of choosing a single-item numerical score as main outcome, see Salaffi *et al*).^55^

#### Secondary outcomes

Anxiodepressive symptoms will be measured using the Hospital Anxiety and Depression Scale (HADS).^56 57^ The HADS consists of 14 self-reported items assessing depressive symptoms (7 items) and anxiety symptoms (7 items). Participants rate their level of agreement on a 4-point Likert scale from 0 (eg, ‘not at all’) to 3 (eg, ‘completely agree’). The total score is calculated by summing responses to all item (ranging from 0 to 42), while subscores for anxiety and depression are obtained by summing responses to relevant items (ranging from 0 to 21). Higher scores indicate more severe anxiety and depressive symptoms.

Quality of life will be assessed using the 12-item SF Health Survey (SF-12).^58^ This scale evaluates eight domains of quality of life (ie, physical, social and usual activity limitations (due to physical or emotional problems), bodily pain, mental health, vitality and general health perception) categorised in two supracategories: physical component and mental component. Participants rate their agreement with various statements using various Likert scales. Higher scores mean better quality of life. After transformation of each supracategory, scores above 50 indicate a better-than-average health-related quality of life (positive outcome), while scores below 50 suggest below-average health-related quality of life (negative outcome).

Fatigue will be measured using the French short version of the Multidimensional Fatigue Inventory–10 Items.^59^ This 10-item questionnaire assesses different dimensions of fatigue (ie, physical fatigue, emotional fatigue, cognitive fatigue) on a 5-point Likert scale. Higher scores mean higher symptoms of fatigue.

At each time of measure, except the first one, a qualitative open-ended item on perceived change, asking participants whether they have noticed any change since the previous session in terms of pain, anxiety and depressive symptoms, quality of life and fatigue will be asked.

Relaxation will be assessed using a French-translated version of the Relaxation State Questionnaire (RSQ).^60^ Originally validated in German and English, this scale will undergo a translation-back translation process to ensure a reliable French version. It consists of 10 self-reported items evaluating momentary relaxation states on a Likert scale from 1 (‘does not apply to me at all’) to 7 (‘applies to me completely’). The RSQ includes four factors: muscular relaxation score, cardiovascular relaxation score, drowsiness and general relaxation score. This scale is considered as well-suited for assessing relaxation states before and after an intervention. Higher scores mean higher relaxation state.

Sociodemographic data (ie, gender, age, marital status, professional status, level of education and duration since diagnosis, diagnosis) will be collected at time 1. Gender and diagnosis will be considered for subgroup analysis, whereas age, marital status, professional status, level of education and duration since diagnosis will be considered as covariables within the analysis.

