**Methods and analysis:**

This study will be a single-centre randomised clinical trial. Participants will be randomly assigned to one of two conditions: one receiving an intervention combining virtual reality and hypnosis, and the other receiving only virtual reality. The effectiveness of the intervention on current perceived pain before and after the intervention (primary outcome) will be evaluated. Secondary outcomes will include anxiety and depressive symptoms, quality of life, relaxation and fatigue. Exploratory analyses will also be conducted to contribute to the emerging literature by examining physiological variables such as heart rate variability, respiratory rate and electrodermal activity during the intervention, and their relationship with primary and secondary outcomes.

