### Intervention

All participants will be provided with a virtual reality headset with an integrated audio system. The Meta Quest Pro, released in 2022, will be used. A tablet connected to the headset will host the hypnosis application developed by Super Splendide (www.supersplendide.com), a company that specialises in the development of virtual reality applications. In collaboration with clinicians, researchers in the field of medical hypnosis and patient partners, Super Splendide is developing an intervention programme that combines VRH. The intervention will be delivered by one of the team members (research assistant adequately trained to communicate with participants, the intervention and the measurement tools) and supervised by VF (postdoctoral researcher in health psychology) and DO (senior researcher and clinical psychologist in pain clinics). Supervisors will be in charge of verifying the correct running of recruitments and data collection and will check those points once every 2 weeks.

For sessions 1 and 2 (ie, time 1 and time 2), participants from both the experimental and control group will not interact with the environment; they will simply be asked to watch and explore a 3D animation of a beach or a forest and relax during the session. The sounds may include the ocean, birds, wind, a crackling campfire and relaxing music. In the control group, sessions 3 and 4 (ie, time 3 and time 4) will consist of the repetition of sessions 1 and 2. In the experimental group, participants will be introduced to hypnosis techniques, the ‘magic hand’ intervention (ie, learning to apply analgesia with their hand) and to an intervention that involves manipulating their pain through an augmented reality script.

A counterbalancing procedure will be applied, respectively for sessions 1 and 2 (ie, beach or forest) and for sessions 3 and 4 (ie, magic hand or pain manipulation).

The fifth session (ie, time 5, follow-up) will correspond to a repetition of the first session (ie, time 1), the aim being to collect data in the exact same conditions to compare baseline and data collected after the intervention.

Given that cybersickness (ie, symptoms occurring when people are exposed to virtual reality) could occur, this variable will be systematically controlled for after each session in all participants with a dedicated questionnaire.^61^

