### Data collection

Consent, questionnaire data and sociodemographic information will be provided by participants on a tablet using the software REDCap. The tablet will be provided by the research assistant in charge of data collection.

Participants will be included prospectively over a 6-week period. Participants will be received five times: the first four sessions (ie, time 1, time 2, time 3, time 4) occurring at a week’s interval, and a fifth session, corresponding to a follow-up session, occurring 3 weeks after the fourth session (ie, repetition of the first session).

After providing their informed consent, participants will be assigned to the previously randomly determined group (ie, the experimental group receiving the intervention or the control group) using the online tool Research Randomizer.^62^ All participants will be asked to avoid caffeinated beverages within 4 hours before the study, to avoid smoking 2 hours before the study and to avoid consuming any stimulants in general.

Participants will be received at Maisonneuve-Rosemont Hospital (Montreal, Quebec, Canada) and seated in a designated study room. This room provides a controlled, quiet environment with a comfortable seat. Before the first session, participants will complete a sociodemographic and clinical questionnaire. Participants will answer questionnaires assessing subjective variables of interest before and after each session (ie, time 1, time 2, time 3, time 4 and time 5). Physiological measurements will be taken from 10 min before the beginning of the intervention.

Figure 1 displays a schematic representation of the procedure.

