### Power analysis and statistical analysis

Quantitative variables will be expressed as mean±SD and categorical variables as frequency and percentages. The impact of the intervention on outcomes of interest will be based on a univariate approach followed by a multivariate approach employing ad hoc model, depending on the structure of the data. Only variables with p<0.20 in the univariate analysis will be considered in the multivariate model. All inferential tests will be two-tailed with a significance level equal to 0.05.

An a priori power analysis was conducted for an analysis of variance (repeated measures, between factors) using the G*Power V.3.1.9.7 software considering current perceived pain as measured with the BPI-SF as main outcome. The effect size *f* was set to 0.25 (medium effect size),^63 64^ the α error risk to 0.05 and the β factor to 0.80. The resulting sample size was calculated as n=82.

As stated in the literature,^65^ an attrition risk should be considered for which an over-recruitment is recommended at time 1 to maintain the required sample size for statistical power. In that sense, a total attrition rate of 20% is expected, leading to recruitment of 98 participants at time 1. Recruitment will be stopped once this targeted sample size is reached. Missing data will be handled by proceeding to multivariable imputation.

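### Baseline pain is not named as a covariate, and entry to the model depends on a p<0.20 screen; prespecifying the pre-session time-1 score would add precision at no cost

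*Protocol article*

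**What the plan says.** Four parts of the protocol article bear on this.

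- **Covariates.** The last paragraph under Secondary outcomes sorts the sociodemographic data by use. The listed covariates are these: "age, marital status, professional status, level of education and duration since diagnosis will be considered as covariables within the analysis". The two remaining variables, gender and diagnosis, are set apart for subgroups. Baseline pain is in neither group.
- **Model.** Power analysis and statistical analysis describes a "univariate approach followed by a multivariate approach employing ad hoc model, depending on the structure of the data". It admits variables to the multivariate step only at p<0.20 in the univariate step. The sample size comes from a repeated-measures ANOVA testing the between-groups factor.
- **Outcome.** Under Primary outcome: "The main criteria will be defined as the score of current perceived pain in the more painful hand". The abstract adds that "current perceived pain before and after the intervention (primary outcome) will be evaluated".
- **Availability of baseline.** Under Data collection: "Participants will answer questionnaires assessing subjective variables of interest before and after each session". Under Intervention, session 5 repeats session 1 in order to "collect data in the exact same conditions to compare baseline and data collected after the intervention".

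**The concern.** The trial collects baseline pain from everyone and relies on it for its before-and-after question, yet it is not among the variables named for adjustment. The article does list other covariates, and it gives a data-driven rule for which variables enter the model. Nothing in the text secures baseline pain a place as a covariate.

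What is at stake is precision. In a randomised comparison, adjusting for the baseline value of the outcome corrects for chance imbalance and removes the part of the variance that baseline explains. Putting baseline into the outcome vector instead, as a change score or as one level of a time factor, forgoes part of that gain. If a pre-treatment score is averaged into a between-groups test, it also dilutes the treatment contrast.

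**Working it through.** **Inputs from the article:** f = 0.25, two-sided alpha 0.05, power 0.80, N = 82, two groups. For two groups d = 2f = 0.5.

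**Assumptions:** 1:1 allocation (41 per arm), equal variances before and after, and pre-post correlation r. The article states neither the ratio nor r, so r is varied from 0.3 to 0.7.

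**Reproducing N = 82.** For the between-groups factor in a repeated-measures ANOVA with m measurements, lambda = f² × N × m / (1 + (m − 1)r), with 1 and N − 2 degrees of freedom. With m = 4 and r = 0.5, lambda = 0.0625 × 82 × 4 / 2.5 = 8.2 and power is 0.808. At N = 80, lambda is 8.0 and power just under 0.80 (0.798), so 82 is the smallest even total. The article gives neither m nor r. This pair reproduces the figure exactly, but that does not prove it was used. At r = 0.5, m = 2, 3 and 5 give 98, 86 and 78.

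**One post score, N = 82.** The noncentrality is d × √(N/4) / √V = 0.5 × √20.5 / √V = 2.264 / √V, where V is the variance relative to an unadjusted post score:

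- post score alone: V = 1, power 0.61
- change score: V = 2(1 − r), 80 degrees of freedom
- baseline as covariate (ANCOVA): V = 1 − r², 79 degrees of freedom

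| r | V, change | V, ANCOVA | Power, change | Power, ANCOVA |
|---|---|---|---|---|
| 0.3 | 1.40 | 0.91 | 0.47 | 0.65 |
| 0.5 | 1.00 | 0.75 | 0.61 | 0.73 |
| 0.6 | 0.80 | 0.64 | 0.71 | 0.80 |
| 0.7 | 0.60 | 0.51 | 0.82 | 0.88 |

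The variance ratio of change score to ANCOVA is 2(1 − r)/(1 − r²) = 2/(1 + r). It is 1.33 at r = 0.5 and 1.18 at r = 0.7. ANCOVA is ahead at every r below 1.

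**Between-groups test on the average of one pre and one post score, r = 0.5.** The pre score carries no treatment effect, so the expected difference halves to 0.25. The variance of the average is (1 + r)/2 = 0.75. The noncentrality is 0.25 × √20.5 / √0.75 = 1.307, and power is about 0.25.

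**Several post scores.** For the mean of four post scores with equal correlations of 0.5 and the same effect at each, P = (1 + 3 × 0.5)/4 = 0.625. The change analysis has V = P + 1 − 2r = 0.625, and ANCOVA has V = P − r² = 0.375. Power at N = 82 is 0.81 against 0.955. This is illustrative only, because sessions 1 and 2 are the same in both arms.

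**The case against.** The strongest reply is that the quoted sentence only sorts sociodemographic data. Pain is an outcome, so its absence from that list is not a decision to exclude it, and the full model may stand in an analysis plan that is not shown. This is fair as far as it goes: the article does not rule out adjustment for baseline. But it does publish a covariate list and an entry rule, and neither secures baseline pain as a covariate.

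A second reply is that baseline is already used through the repeated-measures structure. This also stands, and it determines the right comparator. A reader might infer that baseline is discarded and that adjusting would raise power from 0.61 to as much as 0.88. The documents do not support that: 0.61 is the power of a single post score with baseline unused, which the article does not describe. At r = 0.7 the gain over a change score is from 0.82 to 0.88.

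A third is that a screen on association with the outcome would usually let baseline through. At r = 0.3 and n = 82 the test statistic would be about 0.3 × √80 / √0.91 = 2.8. That is true if baseline is a candidate, but the article does not name it as one, and prespecification removes the dependence on the data.

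Three further inferences should be resisted.

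- **The listed covariates are weakly prognostic or waste degrees of freedom.** The article gives no figure on prognostic strength, and age and duration since diagnosis are not social variables. They are only considered, subject to the screen. Even 12 extra parameters explaining nothing leave power for a single post score at 0.61.
- **Diagnosis is barred from the main model, at a known cost.** Two diagnoses are pooled (the criterion is "having a diagnosis of inflammatory arthritis or osteoarthritis causing invalidating chronic pain"), but use in subgroups does not exclude a main effect, and no gain can be computed from the article.
- **Averaging later pre-session scores would give a better baseline.** Those scores come after randomisation, in participants whom the article says cannot be blinded, so adjusting for them could bias the estimate.

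**Conclusion.** The point holds in a limited form. The article lists covariates and an entry rule without naming baseline pain, and the design it implies probably uses baseline only as a repeated outcome value. Relative to a change score, prespecified adjustment adds about 18 percentage points of power at r = 0.3, 12 at 0.5, 9 at 0.6 and 6 at 0.7. Relative to a between-groups average that includes the pre-treatment score, the gain at r = 0.5 is from about 0.25 to 0.73.

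These figures rest on assumed correlations, 1:1 allocation, d = 0.5 and one post score. The direction does not depend on r; the size does. The comparison remains valid without the adjustment. In a phase II trial of 82 evaluable participants, the precision is still worth having because it costs nothing.

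**What to change.** State, under both Secondary outcomes (where the covariates are listed) and Power analysis and statistical analysis, that each continuous outcome is analysed with its own pre-session time-1 value as a prespecified covariate, entered regardless of the p<0.20 screen. Both places need the change, because an addition to the list alone would leave the screen in force. Use the time-1 pre-session score only, not an average with later sessions.

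Diagnosis may be added as a main effect, without claiming a quantified gain. The other listed covariates need not be removed on the grounds considered here.

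The cost is one sentence in each section. No new data or visits are needed, and the sample size need not change.

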#### Exploratory outcomes

Given the intervention will be led in addition to standard medical care, information regarding antalgic, anxiolytic and antidepressant treatments will be gathered by two means: (1) by consulting medical records (ie, frequency of pharmaceutical dispensing) and (2) by asking participants what medication they consume and their weekly intake.

Physiological activity will be collected using the Biopac MP200-WS system (Biopac Systems, Goleta, California, USA), supplemented by two additional dedicated portable devices. Heart rate will be recorded using a Bionomadix RSP & ECG module (wireless transmitter and RPEC-R amplifier). Two disposable adhesive electrodes will be placed on the participants’ right and left clavicles and a third one on the chest. Heart rate variability will be derived from the data. A respiratory effort transducer (XDCR) will be used to collect respiratory rate. This belt-like device will be positioned around the ribcage at the sternum level. Finally, electrodermal activity will be recorded using the Biodynamix EDA module, which includes a plethysmograph placed on the participants’ index finger.

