### Objectives

The main objective of the present study is to evaluate the effectiveness of a VRH intervention in reducing pain experience in patients with chronic pain. Given the prevalence of chronic pain in the ageing population and that arthritis-related pain is among the most common conditions leading to those symptoms, this population was chosen to test the intervention. This will be achieved by comparing an experimental group, receiving the VRH treatment, to an active control group. It is expected that the subjective and physiological pain scores of individuals who received the intervention will indicate lower levels of pain than those who did not receive the intervention. It is also expected that pain scores of individuals who received the VRH intervention will show a significant reduction in pain perception between the first and last treatment session, with this effect remaining stable over time (ie, 3 weeks after the final session).

A secondary exploratory objective is to observe the impact of VRH treatment on quality of life and anxiety-depressive symptomatology. Exploratory objectives are to explore the effects of the intervention on physiological activity and on medication consumption.

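### The record-based medication measure counts dispensings without strength or quantity, which makes it a coarse index of consumption over six weeks

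*Protocol article*

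**What the plan says.** The Objectives section of the protocol article states: "Exploratory objectives are to explore the effects of the intervention on physiological activity and on medication consumption".

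Under Exploratory outcomes, "information regarding antalgic, anxiolytic and antidepressant treatments will be gathered by two means". The first is "by consulting medical records (ie, frequency of pharmaceutical dispensing"). The second is "by asking participants what medication they consume and their weekly intake".

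Three further statements set the time available for an effect to show:

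- Data collection: "Participants will be included prospectively over a 6-week period". Four sessions are held a week apart, and a fifth takes place three weeks after the fourth.
- Intervention: both arms have the same kind of nature scenes at sessions 1 and 2. After that, "In the control group, sessions 3 and 4 (ie, time 3 and time 4) will consist of the repetition of sessions 1 and 2", while the experimental arm moves on to hypnosis content.
- Blinding and allocation concealment: participants cannot be blinded to their group; the data analysts are.

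**The concern.** The objective concerns how much medication people take. The record-based measure is glossed, with *ie* rather than *eg*, as "frequency of pharmaceutical dispensing". A frequency of dispensing says how often a pharmacy handed something over. It does not say which strength, how many units, or how many days they were meant to last.

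Three consequences follow if the gloss is applied as written. Two people with the same daily intake can have different counts because one collects a longer supply. A person who cuts intake part-way through a short window may show the same count as before. A change of strength dispensed at the same interval leaves no trace.

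At stake is how informative the records can be. They are the only source here that does not depend on the report of participants who know their group. Reduced to a count, they are a weak check on the self-report.

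**Working it through.** The article gives no figure for the medication outcome, so there is nothing to reproduce. The check asks how a count of dispensings behaves over the trial's own timeline.

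**Inputs from the article**

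- Window: 6 weeks = 42 days (Data collection). No separate window for the records is stated, so the participation period is used.
- Divergence of the arms: session 3. With weekly sessions at days 0, 7, 14 and 21, that is day 14.
- Time left for an effect: 42 − 14 = 28 days.

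**Assumptions, not in the article**

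- Supply length S of 30, 60 or 90 days.
- Stock left at day 0 spread evenly between 0 and S.
- A refill only when stock runs out.
- Intake halved from day 14.

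**Step 1: true change in intake.** In units of a usual day's intake, the window total is 42 without a change and 14 + 0.5 × 28 = 28 with it. The fall is (42 − 28)/42 = 33%.

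**Step 2: chance that one person's count does not move.** The count changes only if a refill falls due between cumulative intake 28 and 42, a stretch of 14. For S of at least 14 that has probability 14/S, so P(unchanged) = 1 − 14/S.

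**Step 3: mean counts.** The expected number of fills is total intake divided by S, that is 42/S without the change and 28/S with it.

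| Supply | P(unchanged) | Mean fills, no change | Mean fills, halved from day 14 | Fall in mean |
|---|---|---|---|---|
| 30 days | 16/30 = 53% | 1.40 | 0.93 | 33% |
| 60 days | 46/60 = 77% | 0.70 | 0.47 | 33% |
| 90 days | 76/90 = 84% | 0.47 | 0.31 | 33% |

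The mean falls by the same proportion as intake, because (42/S − 28/S)/(42/S) = 14/42 whatever S is.

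**Step 4: noise from refill timing alone.** At identical intake and a 30-day supply, 60% of people show one fill and 40% show two, purely by when they last collected. The SD is √(0.4 × 0.6) = 0.49, against a mean shift of 14/30 = 0.47. At 60 days (30% with no fill, 70% with one) the SD is √(0.3 × 0.7) = 0.46 against 14/60 = 0.23. At 90 days (53% and 47%) it is √(0.53 × 0.47) = 0.50 against 14/90 = 0.16. A mixture of supply lengths adds more spread, since expected fills at identical intake run from 1.40 to 0.47.

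**Step 5: sensitivity of P(unchanged).**

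| Change in intake | 30 days | 60 days | 90 days |
|---|---|---|---|
| 25% cut from day 14 (stretch 7) | 23/30 = 77% | 53/60 = 88% | 83/90 = 92% |
| 50% cut from day 14 (stretch 14) | 53% | 77% | 84% |
| 50% cut from day 0 (stretch 21) | 9/30 = 30% | 39/60 = 65% | 69/90 = 77% |

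With 7-day dispensing the count follows intake: 42/7 = 6 fills against 28/7 = 4.

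**Step 6: the case outside the model.** If the strength or quantity dispensed changes while the refill interval stays the same, or if refills are automatic, the count is unchanged in every patient and the mean does not move either.

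**The case against.** The strongest reply is that the same sentence also collects self-reported weekly intake, which measures consumption directly. A reader might infer that consumption is derived from the records alone, or that the objective cannot be answered. The article supports neither, because data that address the objective are already planned.

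Second, the article describes data collection. It does not say that fill counts will be analysed as consumption or that the two sources carry equal weight. Which source defines the variable, and how disagreements are settled, may properly stand in a fuller document, so silence on that is not held against the plan. What remains is the gloss itself, which fixes what is taken from the records.

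Third, a reader might take the 53% to 84% to mean that the trial would miss most real changes. Those percentages describe individuals. Under the same model the arm means fall in step with intake. Supply length at entry is balanced in expectation by randomisation, so it adds variance and not a systematic difference between arms. This stands, and it reduces the concern to lost precision plus the special case in step 6.

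Fourth, supply length, refill behaviour, and the size and timing of any change are all assumed. That also stands; the results range from 30% unchanged to 92%, and weekly dispensing would track intake well.

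**Conclusion.** The point holds in a limited form. The stated record-based measure does not match the quantity named in the objective, because a count of dispensings omits strength, quantity and days' supply. Over 42 days, with 28 days of contrast between the arms, it is coarse. For intake halved from day 14, an individual's count stays the same in 53%, 77% or 84% of cases at assumed supplies of 30, 60 or 90 days.

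If people refill only when stock runs out, the cost to the randomised comparison is mainly precision. The comparison is misled only where the amount dispensed changes without a change in refill interval, and the article gives no basis for saying how often that would happen. The outcome is exploratory, so this is a cheap improvement and not a flaw in the trial's main inference.

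**What to change.** In Exploratory outcomes, name self-reported weekly intake as the exploratory consumption measure: drug × unit dose × units taken in the past 7 days, compared between arms at time 5 with adjustment for time 1.

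From the records, extract drug, strength, quantity, days' supply and date at each dispensing in place of frequency alone. Use the amount dispensed as a supportive analysis and cross-check. The records should be kept and not dropped, since they do not depend on reports by unblinded participants.

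The cost is a change of wording and a few more extraction fields, with no extra visits. The remaining weakness is that the main measure relies on self-report by participants who know their group, which is why the supportive analysis matters.
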